### Dissemination

The results of the trial will be published regardless of the direction of effect. Communications will be presented at specialized conferences and reports will be submitted to peer-reviewed medical journals.

### Quality control

A clinical research associate mandated by the sponsor will regularly visit each study center, when the research is set up, once or several times during the course of research, according to the rhythm of the inclusions and at the end of the research. During these visits, and in accordance with the monitoring plan, the following will be reviewed:

#### Informed consent

Respect of the research protocol and procedures defined in itQuality of the data collected in the report file: completeness, accuracy, missing data, consistency of data with source documents (medical records, appointment books, original laboratory results, etc.)

All visits will be subject to a written monitoring report.

### Confidentiality of data

In accordance with the statutory provisions in place (the French Public Health Code), persons having direct access to source data will take every precaution required to ensure the confidentiality of information relating to investigational medicinal products, studies, and participants, notably concerning their identity, as well as the results obtained. These persons, like the investigators themselves, are subject to professional confidentiality.

During the clinical study or at its conclusion, data regarding participants that is collected and sent to the sponsor by the investigators (or all other specialists involved) will be anonymized. At no point will the names of participants or their addresses appear unencrypted.

Only the first letters of the first name and full name of included patients will be recorded, followed by a specific research number indicating the rank of inclusion and the origin of the investigator site.

The sponsor will ensure that each study participant has given their consent for access to their personal data, which is strictly required for study quality control.

### Data and Safety Monitoring Board (DSMB)

The DSMB is an independent group of experts that advises the study investigators. The members of the DSMB serve in an individual capacity and provide their expertise and recommendations. The primary responsibilities of the DSMB are to (1) periodically review and evaluate the accumulated study data for participant safety, study conduct and progress, and, when appropriate, efficacy, and (2) make recommendations concerning the continuation, modification, or termination of the trial. The DSMB considers study-specific data as well as relevant background knowledge about the patient population under study.

The DSMB is responsible for defining its deliberative processes, including event triggers that would call for an unscheduled review, stopping guidelines, unmasking, and voting procedures prior to initiating any data review.

The study DSMB consists of three independent experts, inclduing one expert in the clinical aspects of the stressed/injured patient population; one biostatistician with expertise in current clinical trial conduct and methodology; and one expert in psychotherapeutic EMDR interventions.

The DSMB has been appointed prior to study initiation.

### Premature withdrawal from the study and withdrawal of consent

The participant has the right to withdraw from the research at any time. If participants decide to withdraw from all components of the study, they are no longer followed up in the protocol. Premature withdrawal from the research strategy must be notified promptly to the Steering Committee. The reasons for and the date of withdrawal must be documented. The withdrawal of consent is a decision by a participant to reconsider their decision to participate in the research and to assert their right to withdraw consent at any time during follow-up, without resulting in any prejudice thereby and without having to justify it. When a participant withdraws consent for participation in the research, data already collected for this patient will be kept for analysis.

### Protocol deviations

Deviations can affect all aspects of a research protocol such as inclusion, monitoring, measurement of endpoints, and treatment process. All deviations must be documented by the investigator and discussed by the Steering Committee and Data Management Center.

Even in the event of deviation from the protocol, participants must be monitored until the date planned in the protocol.

### Archiving study documents and study data

The protocol and any changes to the protocol, report files (copies), source files of participants who gave consent, and all other documents and correspondence related to the research will be archived in accordance with good clinical practices for a period of 15 years following the end of the research. The original informed consent forms of participants will be archived for a period of 30 years following the end of the research.

### Ethical approval

The sponsor and the investigator(s) undertake the responsibility to ensure that the research is conducted in compliance with Law no. 2012–300 on research involving human participants of 5 March 2012, in accordance with Good Clinical Practices (I.C.H. version 4 of 9 November 2016 and Decision of 24 November 2006), and the Declaration of Helsinki.

The research will be conducted in accordance with the present protocol. Except in emergency situations requiring specific medical procedures, the investigator undertakes the responsibility to comply with the protocol in all respects, particularly with regard to the collection of consent, and the reporting and monitoring of serious adverse events.

This research project has received positive endorsement from the French CPP (Comité de protection de Personnes Ouest II - Angers). N° RCB = 2017-A01462–51 – N°CPP = 2017/36.

The University Hospital of Bordeaux, the sponsor of this research, has taken out a civil liability insurance contract with Gerling-Biomedicinsure in accordance with the provisions of the public health code.

The data recorded in the course of this research shall be subject to computer processing on behalf of INSERM U1219 Bordeaux Population Health Research Center in compliance with Law No. 78–17 of 6 January 1978 relating to data processing, files and freedoms, as amended by Law 2004–801 of 6 August 2004.

This research project falls within the framework of the “Reference Methodology” (MR-001) in application of the provisions of article 54, paragraph 5 of the amended law of 6 January 1978 relating to information, files and freedoms. This change was approved by the decision of 5 January 2006, updated on 21 July 2016. The INSERM U1219 Bordeaux Population Health Research Center has signed a commitment to comply with this “Reference Methodology”.

A specific request for clearance will be submitted to the Commission Nationale Informatique et Liberté (CNIL) in order to obtain the authorization to use the national social security ID to retrieve medication data at 3 and 12 months.

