### Inclusion criteria

All patients attending the adult ER of one of the study sites following an event that led to an injury, or with a new acute medical condition, will be assessed for inclusion. The inclusion criteria are as follows:Age 18 and aboveConscious, able to provide informed consent, able to understand study procedures and to comply with them for the entire length of the study; French speakerInjured, whatever the cause of injury (the event causing the injury must have occurred in the past 12 h) or experiencing a medical event associated with an acute medical condition and presenting for the first time to the ER for this reasonScore resulting from the screening tool > 1: female: + 1, taking at least one anxiolytic treatment: + 1, perceived health status prior to admission: excellent, very good 0; good: + 1; poor: + 2; bad + 3Affiliated to the French insurance system

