**Fig. 2 Fig2:**
[figure not shown]
Schedule of enrolment, interventions, and assessments

A set of three items will be recorded for each injured patient, including sex (+ 1 for female), perceived health status prior to admission (excellent, very good: 0; good: + 1 poor: + 2; bad: + 3), current use of anxiolytics/antidepressants (+ 1 if yes).

To be enrolled in the study, the patient will need to score above a pre-defined threshold of 2 on the scoring procedure based on the three items and designed to select patients at risk for PCLS. The score has been developed using data from the Pericles study and validated on data of the SOFTER Pilot 1 and 2 studies.

Patients fulfilling inclusion criteria and assessed as at risk for PCLS will be presented with the objective and procedures and invited to sign an informed consent form. A screening log will be filled in to describe reasons for ineligibility and for non-participation of eligible candidates.

The randomization procedure for assigning a participant to an intervention group will then be performed and the results will be recorded in the Shared Study Monitoring System. Electronic block randomization will be stratified according to study center. Block sizes will be randomly modified and kept secret.

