### Data analyses

Descriptive and inferential statistical methods will be used to analyze the outcomes and other study data. Confounding variables will include cause of admission (injury versus medical), age group, and sex. The analyses will be conducted as intent-to-treat for primary endpoint and per-protocol for secondary analyses. Randomization codes will only be revealed at the end of the analysis.

Primary analyses will be conducted using a Fisher exact test. A stratified analysis will be carried out considering study center and PCLS risk score. For other variables, Wilcoxon test will assess differences for continuous variables and Fisher exact test for categorical variables.

Differences between patients who completed the study and those who were lost to follow-up will be assessed for all variables.

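### Psychotropic use at 3 months is to be tested with an unadjusted Fisher exact test although use at entry is recorded for every patient; the test is valid but pools continuing with new users and loses power

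*Protocol article*

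**What the plan says.** All references are to the protocol article.

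- **Methods/design** lists psychotropic medicine use at 3 months, taken from insurance drug delivery data, as the last secondary outcome. It is plain use, not new use or change.
- **Data analyses** fixes the test for outcomes other than the primary: "For other variables, Wilcoxon test will assess differences for continuous variables and Fisher exact test for categorical variables".
- The same section names covariates: "Confounding variables will include cause of admission (injury versus medical), age group, and sex". Medication at entry is not among them. It also says "A stratified analysis will be carried out considering study center and PCLS risk score", directly after the sentence on the primary analysis and before the sentence on other variables.
- **Inclusion criteria** score the drug item as "taking at least one anxiolytic treatment: + 1". **Study enrollment procedures and randomization** (text after Fig. 2) words it as "current use of anxiolytics/antidepressants (+ 1 if yes", recorded for each patient assessed.
- On allocation, the enrollment section says "Electronic block randomization will be stratified according to study center". Prior use is not a stratum.
- **Ethical approval** announces a request, still to be submitted, for "authorization to use the national social security ID to retrieve medication data at 3 and 12 months".

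**The concern.** Someone already taking an anxiolytic or antidepressant at the ER visit will often still be taking it 3 months later, for reasons that predate the event. The screening score gives such patients a point, so selection favours them. The planned test puts them in the same two-by-two table as patients who start a drug after the event.

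Two things follow. If EMDR mainly prevents new prescriptions, continuing users add the same count to both arms and shrink the difference. If EMDR also changes use in prior users, the crude table still carries the large between-patient variation due to prior use, which stratification would remove. Either way, a null result on this outcome would be hard to read, although the variable needed to sharpen it is already collected.

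**Working it through.** **The plan's own figures.** The article gives no rate or power for medication use. Its only sample-size figures concern the primary outcome, and they reproduce. For 47% vs 32%, two-sided 5%, 80% power:

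n = [1.96·√(2·0.395·0.605) + 0.842·√(0.47·0.53 + 0.32·0.68)]² / 0.15² ≈ 166 per arm (stated 169).

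Inflation: 169 / 0.80 / 0.95 = 222.4 (stated 223). Below, 223 per arm assumes that the insurance database covers every randomized patient, since it needs no phone contact.

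**Dilution.** Let b be the share of prior users, c the proportion of them still using at 3 months in both arms, and q0 and q1 new use among non-users in control and EMDR.

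- Control rate = b·c + (1−b)·q0; EMDR rate = b·c + (1−b)·q1.
- Risk difference = (1−b)·(q0 − q1).
- Example with b = 0.40, c = 0.90, q0 = 0.20, q1 = 0.10: control 0.36 + 0.12 = 0.48; EMDR 0.36 + 0.06 = 0.42. The risk ratio moves from 0.50 to 0.88 and the difference from 10 to 6 points.

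**Power by simulation.** All rates are assumptions. 223 per arm, two-sided 5%; repeat runs move a cell by one or two points.

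*Scenario A, EMDR acts in both groups:* use 85% vs 75% in prior users, 15% vs 7.5% in others.

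| Prior users | Crude Fisher | Stratified by prior use (CMH) |
|---|---|---|
| 10% | 52% | 72% |
| 20% | 46% | 71% |
| 30% | 43% | 73% |
| 40% | 41% | 73% |
| 50% | 41% | 73% |
| 60% | 45% | 74% |

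Across repeat runs the stratified figures span 71-75%. With 169 per arm and 30-60% prior users, power is about 32-35% crude and 60-62% stratified.

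*Scenario B, EMDR acts on new use only:* 80% of prior users continue in both arms; new use 15% vs 7.5%.

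| Prior users | Crude Fisher | Stratified (CMH) | Fisher, non-users at entry only |
|---|---|---|---|
| 10% | 41% | 59% | 64% |
| 20% | 28% | 47% | 57% |
| 30% | 19% | 36% | 52% |
| 40% | 14% | 27% | 46% |
| 50% | 12% | 19% | 38% |
| 60% | 8% | 13% | 31% |

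**Cross-check by normal approximation**, other rates (90% continuing, new use 20% vs 10%, 223 per arm): crude power 84% with no prior users, 45% at b = 20%, 25% at b = 40%. Stratified it is 69% and 47% at those two shares; among non-users only, 76% and 63%.

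**How much is Fisher's conservatism.** At 169 per arm with 20% vs 10% new use, 90% continuing and b = 0 to 40%, Fisher has about 2 to 4 points less power than the uncorrected test. That explains a small part of the crude-to-stratified gap. In Scenario B, the last column compares Fisher with Fisher.

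**Validity.** With no effect (80% use in prior users and 15% in others, in both arms), the crude Fisher test rejects in about 4% of simulated trials.

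**Does the risk-score stratification already cover this?** The total mixes three items. A woman in good health on no drug scores 1 + 1 + 0 = 2; a man in good health on an anxiolytic scores 0 + 1 + 1 = 2. At a higher total, a woman in poor health on no drug scores 1 + 2 + 0 = 3, as does a man in poor health on a drug (0 + 2 + 1). Users and non-users share strata under either stated threshold.

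**The case against.** **A reader might infer that continuing users hide any effect, or bias the comparison.** The document does not support that. Prior users balance on average under randomization, and the crude test holds its error rate. A chance imbalance of 1.96 SD in prior use (about 9 points, from √(2b(1−b)/223) ≈ 0.043-0.047) would shift the difference by about 9 × (0.80 − 0.15) ≈ 6 points, but the 5% error rate already allows for such events. Prior users who stop because of EMDR also count legitimately under the outcome as defined.

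**A reader might infer that no pre-visit deliveries will be requested.** That rests on one sentence in the ethics section, which may describe when data are extracted rather than the dates they cover. The request is not shown, and look-back windows commonly sit in a full protocol or analysis plan.

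**Adjustment may be intended.** The covariate sentence is not confined to the primary outcome, and an analysis plan could add more. But prior medication is not on the list, the test named for these outcomes takes no covariates, and the risk-score stratification is placed with the primary analysis.

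**The rates are invented and the prior-user share is unknown.** This stands. The drug item is not required for entry: under the inclusion criteria (score above 1), a woman in good health or anyone in poor health qualifies without it. The enrollment section instead requires patients to "score above a pre-defined threshold of 2", so the share cannot be derived.

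**Stratifying does not rescue the outcome if only new use responds.** This also stands: 13-59% is still low. Hence the supporting analysis among non-users.

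**Conclusion.** The point holds as a loss of precision on one secondary outcome, not as bias. The article names an unadjusted test for psychotropic use at 3 months while a likely strong predictor is recorded at screening and left out. With 223 per arm and prior-user shares of 10-60%, assumed rates give about 41-52% power crude against 71-75% stratified if EMDR acts in both groups. If it acts only on new use, the figures are about 8-41% crude, 13-59% stratified and 31-64% among non-users at entry. Stratification gains power at every share examined, but how much depends on the share of prior users and their continuation rate, neither of which is in the document. Whether a pre-visit delivery window is planned cannot be judged from the article. The primary outcome and sample size are not touched.

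**What to change.** In **Data analyses**, state that psychotropic use at 3 months will be compared with stratification by use at entry, as recorded at screening, and by center (Cochran-Mantel-Haenszel, or logistic regression with both terms). Report new use among non-users at entry as a supporting result.

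Reconcile the drug item between **Inclusion criteria** (anxiolytics only) and **Study enrollment procedures and randomization** (anxiolytics or antidepressants), so that the stratifying variable has one meaning. The entry thresholds in the same two places also need reconciling.

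Optionally, if the request described under **Ethical approval** does not already cover it, add drug deliveries in a fixed window before the visit (for example 3 months), so that baseline and outcome come from the same source.

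The cost is a few sentences, to be fixed before outcome data are examined by arm, and at most one more date range in a request that the article describes as not yet submitted. No extra patients, visits or staff are needed.

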## Discussion

The trial is designed to test the impact of early EMDR intervention on PCLS and PTSD in patients presenting to the ER. In 2012, the year when the last national survey in France was undertaken, 10.6 million people attended the ER, some of whom several times, since 18 million visits were recorded that year. The SOFTER 3 study therefore addresses a major public health challenge.

We already described the feasibility of short EMDR sessions in the ED during the SOFTER 2 study [53], which also found a superiority of EMDR versus reassurance versus control. We need to confirm these results in a larger and more diverse population.

## Trial status

The present publication refers to the 4.0 version of the SOFTER 3 protocol dates on 01/02/2018. Recruitment began on January 15, 2018, and is expected to be completed by the June 15, 2018.

## Abbreviations

DSMB: Data Safety Monitoring Board
EMDR: eye movement desensitization and reprocessing
ER: emergency room
ERP: emergency response procedure
PCLS: post-concussion-like symptoms
PCS: post-concussion syndrome
PTSD: post-traumatic stress disorder
R-TEP: recent traumatic episode protocol
SOFTER: SymptOms Following Trauma, Early Response
